# Safety and efficacy of different rotational speed during rotational atherectomy in coronary heart disease patients (RACE): study protocol for a randomized controlled trial

**DOI:** 10.1186/s13063-025-08834-6

**Published:** 2025-04-08

**Keywords:** Rotational atherectomy, High speed, Low speed, Vascular calcification

## Abstract

**Introduction:**

The increasing incidence of coronary heart disease, driven by socio-economic development and population aging, poses significant challenges. Coronary calcification, a major factor complicating percutaneous coronary interventions (PCI), often necessitates rotational atherectomy (RA) for lesion preparation. However, the impact of different RA rotational speeds on procedural and clinical outcomes remains unclear. While low-speed RA (LSRA) has been suggested to reduce intraoperative slow flow, evidence is inconsistent, and the benefits of combining LSRA with high-speed RA (HSRA) are not well established. This study aims to evaluate the effectiveness of different rotational speed protocols to guide clinical practice.

**Methods and analysis:**

This single-center, randomized controlled trial will target patients with severe coronary artery calcification scheduled for RA. An estimated 210 patients will be enrolled based on sample size calculation, randomly assigned in a 1:1:1 ratio to different rotational speed protocols using a random number table. These will include a continuous low-speed rotation (LSRA) group (140,000 rpm), a continuous high-speed rotation (HSRA) group (180,000 rpm), and a high-speed to low-speed rotation (HSRA + LSRA) group (initially 180,000 rpm, followed by 100,000 rpm). The primary endpoint is the incidence of complications during RA, including coronary artery spasm, slow/no reflow, dissection, burr entrapment, guidewire fracture, and perforation. Secondary outcomes encompass intravascular imaging (IVUS or OCT) assessments (detecting calcific ring disruption and measuring the target lesion’s minimum lumen area (MLA) and minimum lumen diameter (MLD)); in-hospital cardiac death, acute stent thrombosis, and heart failure occurrences; and the 1-year incidence of major adverse cardiovascular and cerebrovascular events (MACCE).

**Discussion:**

The RACE study evaluates the impact of different rotational speeds in coronary rotational atherectomy, aiming to provide guidance for clinical practice. The findings may help standardize RA procedures and inform future clinical guidelines, improving procedural consistency and patient outcomes.

**Registration number:**

ChiCTR2300076194. Registered on September 27, 2023.

## Introduction

With the progression of socio-economic development and an aging population, the incidence of coronary heart disease (CHD) is steadily increasing. Against this backdrop, the issue of coronary artery calcification (CAC) has become increasingly prominent, especially among middle-aged and older adults. Epidemiological data indicate that in adults aged 45 to 84, the prevalence of CAC can be as high as 70.4% [1]. Among patients undergoing percutaneous coronary intervention (PCI), approximately 18 to 24% exhibit moderate to severe calcification [2]. Studies have shown that patients with severe CAC face a higher risk of major adverse cardiovascular and cerebrovascular events (MACCE), including death, myocardial infarction, target vessel revascularization, and in-stent thrombosis [3–7]. Therefore, effectively managing CAC is crucial for improving the outcomes of PCI.

In recent years, with the increasing emphasis on “optimizing PCI,” pre-procedural vessel preparation for PCI has garnered widespread attention. In this context, calcific lesions have become as a significant challenge in cardiovascular intervention. Despite advancements in PCI techniques, the presence of CAC remains a major barrier to both short-term and long-term success of treatments. Rotational atherectomy (RA) is a key technique for managing calcified coronary lesions, offering distinct clinical benefits. By modifying calcific plaques, facilitating stent delivery, and increasing the luminal area, RA enhances PCI success rates [8]. The PROTECT II trial studied RA in high-risk PCI and found that while essential for severe calcific lesions, it may also increase the risk of perioperative myocardial infarction [9]. Among procedural variables, burr rotation speed is considered a key determinant of both procedural outcomes and complication rates [10]. However, the optimal strategy for rotation speed remains undefined. Expert opinions on this issue vary across different regions and clinical practices [11–14]. Low-speed rotational atherectomy (LSRA) has been reported to reduce intraoperative slow flow, but the supporting evidence is inconsistent, and no consensus has been reached on its clinical benefits [15–17]. Recent studies have reported that a combination strategy of LSRA and high-speed RA (HSRA) is a safe and feasible approach for managing severely calcified lesions in clinical practice, yet its advantage over conventional methods remains unclear [18]. While LSRA following HSRA has been associated with greater lumen gain compared to continuous HSRA, conflicting findings exist, and its long-term impact is not well established [18, 19]. Most existing studies are retrospective or observational, and large-scale trials on the optimal rotational speed for better procedural success and outcomes are lacking.

Our previous retrospective studies have identified differences in perioperative outcomes among patients undergoing RA at different rotational speeds [10, 20]. However, the optimal and safest burr rotation speed remains uncertain, highlighting the need for further prospective research to establish a standardized approach.

To address this gap, the RACE trial aims to evaluate the safety and efficacy of different rotational speed protocols by analyzing their impact on perioperative complications and long-term prognosis in patients with CHD.

## Methods

### Study design

This is a single-center, randomized controlled study focusing on patients with CHD who have significant CAC and are candidates for RA. The objective of the study is to examine differences in perioperative complications and long-term prognosis among various rotational speed protocols in these patients. We plan to continuously recruit participants at a tertiary A-grade hospital in Anhui, China, which is renowned for its large patient population with cardiovascular diseases and advanced medical technology. Patients who require RA treatment and meet the specific inclusion criteria (Table 1) will be enrolled in the study. Prior to undergoing RA, the principal investigator (PI) will verify patient eligibility and obtain written informed consent.

**Table 1 Tab1:** Eligible criteria

Inclusion criteria • Age ≥ 18 years old • The presence of severe coronary calcification was evaluated utilizing one of the following methods: ➢ CAC assessed as severe based on semi-quantitative scoring ➢ IVUS detection of calcific lesions exceeding 270° in arc ➢ IVUS identification of prominent calcific nodules protruding into the lumen ➢ OCT assessment scoring calcification as 4 points ➢ OCT identification of prominent calcific nodules protruding into the lumen ➢ Inability of the balloon to pass or fully expand the lesion
Exclusion criteria • Age > 80 years • Severe left ventricular dysfunction [LVEF ≤ 30%] • Lesions where the rotational atherectomy guidewire cannot pass • Lesions rich in thrombus • Venous bridge vascular lesions • Lesions with acute angles ≤ 90° • Severe spiral dissection • Immediate rotational atherectomy following stent placement • Pregnant or breastfeeding women • Anticipated lifespan < 1 year • Inability to comply with follow-up

*CAC* Coronary Artery Calcification, *OCT *Optical Coherence Tomography, *IVUS *Intravascular Ultrasound, *LVEF *Left Ventricular Ejection Fraction

Lesions with acute angulation (≤ 90°) were excluded as studies have identified severe angulation as an independent predictor of procedural and clinical failure in RA [21]. Immediate RA following stent placement was excluded due to the high risk of burr entrapment and suboptimal long-term outcomes reported in previous studies [22–25]. *CAC*, coronary artery calcification; *OCT*, optical coherence tomography; *IVUS*, intravascular ultrasound; *LVEF*, left ventricular ejection fraction.

It is anticipated that 210 patients who meet the inclusion and exclusion criteria will be randomly assigned in a 1:1:1 ratio to three different rotational speed groups: a continuous low-speed rotation (LSRA) group (140,000 rpm), a continuous high-speed rotation (HSRA) group (180,000 rpm), and a high-speed to low-speed rotation (HSRA + LSRA) group (initially 180,000 rpm, followed by 100,000 rpm). The study includes a 12-month follow-up period. Research protocols and documents have been distributed to relevant researchers. Recruitment began on October 1, 2023, and will continue until the estimated number of patients is reached, with the study expected to be completed within 3 years.

This study protocol has been approved by the Medical Research Ethics Committee of the First Affiliated Hospital of the University of Science and Technology of China (Anhui Provincial Hospital) under approval number 2023-KY- 076.

### Randomization

Eligible patients who provide informed consent will be randomly assigned in a 1:1:1 ratio to one of three rotational speed groups for RA treatment (Fig. 1). To ensure unbiased random allocation, a computer-generated random number table was created prior to the commencement of the study. Patients will be assigned sequentially based on this table to one of three groups: LSRA, HSRA, or HSRA + LSRA, maintaining a 1:1:1 distribution to ensure group balance. Once a patient meets the inclusion criteria, the assigned study personnel will disclose the randomization result but will not be involved in data collection or follow-up. To minimize bias, outcome assessors will remain blinded to the treatment allocation. These assessors, responsible for evaluating primary and secondary endpoints, will not be aware of the specific intervention each patient receives. Randomization data will be securely stored and managed by an independent data management team, ensuring blinding until the completion of data analysis. This methodology ensures an objective assessment of the safety and efficacy of different RA rotational speed protocols, offering valuable insights for optimizing treatment strategies in coronary heart disease.

**Fig. 1 Fig1:**
[figure not shown]
LSRA, low-speed rotation; HSRA, high-speed rotation; HSRA + LSRA, a high-speed to low-speed rotation; OCT, optical coherence tomography; IVUS, intravascular ultrasound; PCI, percutaneous

### Clinical procedures

Our center utilizes the Siemens DTC (or PHILIPS FD1010) angiography system for coronary angiography and interventional therapy. The Rotablator System (Boston Scientific Corporation, Natick, MA, USA) was used for all the RA procedures. Prior to the procedure, patients were treated with aspirin (100 mg per day) and thienopyridine (clopidogrel 75 mg daily or ticagrelor 100 mg twice daily). In addition, normal heparin (70–100 units/kg) was administered intravenously during the procedure to achieve an appropriate activated clotting time (250 s). Percutaneous coronary intervention was performed at the operator’s discretion. In previous studies [26], we observed that higher experience in RA might be linked to worse outcome in PCI via femoral approach in both stable angina and acute coronary syndrome settings. However, the specific approach should still be determined based on the characteristics of the patient’s specific lesions and the conditions of the peripheral vascular pathways. Catheters up to 7 F in diameter were used to exchange a 0.009-inch (1 inch = 2.54 cm) rotating wire flexible disk to the distal end of the target lesion with the help of a Finecross or Crossair microcatheter. Each RA session lasted less than 30 s, with a 60-s interval between each RA. During the RA procedure, a continuous pressurized drip of plain heparin nitroglycerin flushing solution was administered. Noncompliant balloon dilation and stent placement were performed following the RA procedure, depending on the lesion characteristics. Patients who developed bradyarrhythmias after RA received both a strong cough and intravenous atropine. Atropine and a temporary pacemaker were prepared for patients with right coronary artery or systolic branch predominance. Implantation of intra-aortic balloon counter pulsation (IABP) depends on the judgment and guidance of the supervising cardiologist. Following the completion of rotational atherectomy, a follow-up coronary angiography was performed. In cases of vascular spasm, intracoronary nitroglycerin or sodium nitroprusside was administered via the catheter to relieve the spasm.

This study will assess the effectiveness of coronary RA using IVUS and OCT, which provide detailed imaging of lesion structure and treatment outcomes. IVUS is a technique that uses high-frequency sound waves to visualize the inner walls of blood vessels [27]. IVUS utilizes high-frequency sound waves to visualize the inner walls of blood vessels, allowing us to accurately measure the degree of stenosis and the composition of the plaque. In this study, IVUS will assess intimal lumen diameter and plaque morphology before and after RA. This will help clarify how different rotational speeds affect the vessel wall and plaques. On the other hand, OCT uses near-infrared light to capture high-resolution images of the vessel lining [28]. OCT can provide higher resolution images than IVUS, especially in assessing intima and plaque surface characteristics. In this study, OCT will be used to assess endovascular surface features after RA treatment, including plaque tears, stenting effects, and possible vessel damage. By combining IVUS and OCT, we will be able to comprehensively evaluate the effects of RA treatment at both macroscopic and microscopic levels. This information will provide important clinical data for evaluating the safety and efficacy of different rotational speeds, thus contributing to optimize the use of RA in the treatment of coronary artery disease (CAD).

### Planned outcomes

The primary focus of this study is to investigate the safety and efficacy of using different rotational speeds in coronary rotational atherectomy. The main endpoint is the incidence of complications during the atherectomy procedure. Secondary endpoints include assessments through intravascular imaging, in-hospital adverse cardiovascular events, and adverse cardiovascular events during the 1-year follow-up period (Table 2).

**Table 2 Tab2:** Primary and secondary endpoints

Primary endpoints	
Complications during RA	Coronary artery spasm Slow flow/no reflow Dissection Burr entrapment Guidewire fracture Perforation
Secondary endpoints	
IVUS/OCT	① Calcific ring disruption ② MLA ③ MLD
Adverse events	Cardiac death Acute stent thrombosis Heart failure
MACCE	Cardiac death Non-fatal myocardial infarction Ischemia-driven revascularization TIA

In IVUS, calcific ring disruption is defined as a loss of continuity in the calcified plaque, presenting as fissures, defects, or fractures along the plaque margins. In OCT, it is identified by cracks, defects, or fractures within the calcified region, resulting in surface irregularities or cavitations. *RA*, rotational atherectomy; *MLA*, minimum lumen area of target lesion; *MLD*, minimum lumen diameter of target lesion; *TIA*, transient ischemic attack; *MACCE*, major adverse cardiovascular and cerebrovascular events; *IVUS*, intravascular ultrasound; *OCT*, optical coherence tomography.

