### Statistical analysis

All data will be statistically analyzed using SPSS version 22.0. Quantitative data will be presented as mean ± standard deviation (± s), with intergroup comparisons made using independent sample *t*-tests. Categorical data will be presented as number (percentage) [*n* (%)], with intergroup comparisons using the χ^2^ test. Logistic regression analysis will be applied to ascertain the correlation between coronary rotational speed and perioperative complications, as well as 1-year MACCE. Considering potential data missing and loss to follow-up, we will mainly use intention-to-treat (ITT) analysis and apply per-protocol (PP) dataset for sensitivity analysis. Besides, we will preset some subgroup analyses (e.g., based on patient age groups or lesion complexity) to verify results’ stability and explore special effect participants. To account for multiple comparisons, family-wise error rate (FWER) control methods will be applied where appropriate. Specifically, Bonferroni correction (adjusting the significance threshold to *α*′ = 0.025) and the Holm-Bonferroni procedure (a stepwise approach that improves statistical power while maintaining FWER control) will be used for primary analyses. To minimize unnecessary tests, only key comparisons (HSRA vs. LSRA; HSRA + LSRA vs. LSRA) will be included. When the sample size is limited, Holm’s method will be preferred over Bonferroni to optimize the balance between statistical power and error control. A *P* value of < 0.05 will be considered statistically significant. All statistical tests will be two-sided.

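### One-year MACCE in Table 2 counts TIA but not stroke, so a non-fatal stroke is not an event in a composite named for cerebrovascular events

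*Protocol article*

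**What the plan says.** The Planned outcomes section, Table 2, gives the components of MACCE as "Cardiac death Non-fatal myocardial infarction Ischemia-driven revascularization TIA". The list is closed: nothing marks the items as examples. The table legend expands TIA as "transient ischemic attack" and MACCE as "major adverse cardiovascular and cerebrovascular events".

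The other clinical row among the secondary endpoints, for in-hospital adverse events, reads "Cardiac death Acute stent thrombosis Heart failure". The primary endpoint consists of procedural complications during rotational atherectomy.

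The abstract names 1-year MACCE among the secondary outcomes. The Statistical analysis section plans a logistic regression of perioperative complications on rotational speed, "as well as 1-year MACCE".

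**The concern.** The composite's name promises major cerebrovascular events, yet its only cerebrovascular component is the transient one. Within that component the order of seriousness is reversed: the milder event scores and the graver one does not. The article offers no reason for this.

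MACCE is the only clinical endpoint listed for the 1-year follow-up, it carries the trial's long-term prognosis objective, and it has its own regression. A patient with a non-fatal stroke and none of the listed events would enter that regression as event-free. A reader of the results would reasonably suppose from the name that stroke had been counted.

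**Working it through.** This is a defect in a definition, so the main check is a comparison of the component lists. The arithmetic only gives a sense of size.

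**1. Does any listed endpoint capture stroke?**

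| Where | Cerebrovascular content |
|---|---|
| Table 2, primary endpoint | None; six procedural coronary complications |
| Table 2, imaging | None; calcific ring disruption, MLA, MLD |
| Table 2, in-hospital adverse events | None |
| Table 2, MACCE | TIA only |

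The word stroke does not occur in the text of the article, including the abstract, the introduction and the abbreviations.

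**2. What the rule does with each event at 1 year**

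- TIA: listed, so it counts.
- Non-fatal stroke: not listed, so it does not count. This needs no assumption.
- Fatal stroke: the death component is cardiac death, not death from any cause. On the usual meaning of cardiac death it does not count. The article does not define the term, so this step is conditional.

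**3. The plan's own figure**

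The only sample size stated is for the primary endpoint. Inputs from the Sample size section: rates of 4%, 14% and 24%, 2 degrees of freedom, α = 0.05, 80% power, 15% dropout.

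- Mean rate = (0.04 + 0.14 + 0.24)/3 = 0.14.
- W = √{[(0.10² + 0² + 0.10²)/3] / (0.14 × 0.86)} = √(0.006667/0.1204) = 0.2353, as stated.
- Noncentral chi-square power with noncentrality N × W²: N = 175 gives 0.802 and N = 174 gives 0.79996, so 175 is reproduced.
- Per group: 175/3 rounds up to 59; 59/0.85 = 69.4, which rounds up to 70; 3 × 70 = 210, as stated.

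None of these inputs involves MACCE, so adding stroke leaves them unchanged.

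**4. Possible size of the gap**

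The article gives no stroke or MACCE rate. The 1-year stroke risks s below are assumptions, for illustration only. Expected strokes = 210 × s; chance of at least one = 1 − (1 − s)^210.

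| Assumed s | Expected strokes in 210 | Per arm of 70 | Chance of at least one |
|---|---|---|---|
| 0.5% | 1.05 | 0.35 | 65% |
| 1% | 2.1 | 0.7 | 88% |
| 2% | 4.2 | 1.4 | 99% |
| 3% | 6.3 | 2.1 | >99% |

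These are all strokes. The number of misclassified patients would be somewhat lower if some also had a listed event, or if fatal strokes were somehow counted under cardiac death.

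**5. Who is already past 12 months?**

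Recruitment opened on October 1, 2023, and 132 patients had been randomized by September 22, 2024 (Trial status). By publication on April 8, 2025, anyone enrolled before about April 8, 2024 had passed the 12-month point. For them the scheduled contact can no longer be used to ask about stroke.

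**The case against.** The strongest reply is that the consequence is small. MACCE is one of several secondary endpoints, the trial is not sized for it, and under the assumed risks the strokes come to roughly two per arm at most. Nothing shows that an arm comparison would change. This stands, and it limits the weight of the point.

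A second reply is that an article condenses the full protocol. That would excuse missing event definitions or adjudication rules. It does not excuse a complete component list that contradicts its label. If the full protocol counts stroke, Table 2 misstates it; if not, the endpoint itself needs amending.

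Several stronger readings are tempting, and the documents do not support them:

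- *Strokes go unrecorded.* A reader might infer this, but the Trial schedule and follow-up section says safety is assessed at 12 months in addition to the endpoints, and Table 3 is not shown. Strokes may be recorded as safety events. What is established is only that they do not count in MACCE.
- *The Introduction contradicts Table 2.* Its list, "including death, myocardial infarction, target vessel revascularization, and in-stent thrombosis", describes what cited studies reported in severe calcification. It does not define this trial's endpoint, and it contains neither stroke nor TIA, so it is no evidence that stroke belongs.
- *The results could not be compared with other reports.* Apart from that background list, the article shows no other study's MACCE definition, so this cannot be established from the text.
- *Every fatal stroke is certainly missed.* That depends on the undefined term cardiac death.

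**Conclusion.** The point holds as a wrongly fixed secondary endpoint. Followed literally, Table 2 scores a TIA as a MACCE and a non-fatal stroke as no event, contrary to the composite's name. The same applies to a fatal stroke, provided cardiac death is read in its usual sense.

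The size cannot be derived from the article. With an assumed 1-year stroke risk of 0.5% to 3%, about 1 to 6 of 210 patients would be misclassified.

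A reader might infer that the omission undermines the trial's main conclusion. It does not: the primary endpoint, its test and the total of 210 are untouched. It affects what the 1-year clinical endpoint means and how its result may be described.

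**What to change.** Before outcomes are analysed, amend the MACCE row of Table 2 so that its cerebrovascular component reads *stroke (ischaemic or haemorrhagic, fatal or non-fatal) or TIA*. Report stroke and TIA separately as well, and apply the definition to all randomized patients, including those enrolled before the amendment. If the full protocol already counts stroke, the same wording corrects the article.

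The costs are small but real:

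- A dated mid-trial amendment of a secondary endpoint, made before outcome analysis so that it cannot appear driven by the data.
- A stroke item on the case report form, if there is none.
- Record review or one recontact for patients already past their 12-month contact, if stroke was not recorded as a safety event. For patients still to reach 12 months, the planned contact suffices.

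No change to the sample size or to the primary analysis is needed.
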